### Intervention

After being diagnosed with prostate cancer, but before a treatment decision has been made, patients in the intervention arm receive access to the online DA. Healthcare providers are instructed to introduce the DA and the study at diagnosis. However, the pragmatic nature of this trial allows hospitals to integrate the introduction of the DA with their standard information provision routines if that follows later due to follow-up diagnostics or an additional consultation with (oncology) nurses. In daily practice, this means that either the urologist or the (oncology) nurse introduces the DA to the patient. To use the DA, patients receive a card from their urologist stating their relevant disease characteristics (PSA, Gleason, and eligible treatment options) and a personal username and password to gain online access to the DA. If a nurse introduces the DA and accompanying access card, the urologist should provide the requested clinical characteristics to the nurse, either by filling in the card or by leaving a note in the patients’ record.

The DA offers a stepwise guidance through the decision process. In the first step, general information about prostate cancer is provided. The second step offers the consideration between active surveillance and curative treatment (surgery or radiotherapy). Values clarification statements are presented in this step to elicit a patient’s preference based on three main differences between AS and curative treatment; acceptance of deferring treatment (*‘I am confident enough that I will be treated on time*, *if necessary’* versus ‘*I do not want to postpone treatment because I do not want to be too late*’), avoiding possibly unnecessary treatment (‘*If treatment might be unnecessary, I would rather wait*’ versus ‘*I prefer treatment, even if it might be unnecessary*’) and the acceptance of treatment side effects (*‘I find possible treatment side effects like erectile and urinary dysfunctions difficult to accept’* versus ‘*I find the possible treatment side effects acceptable’*). Each statement is related to one of the two offered treatment alternatives in this step. On a slider scale, patients can indicate for each set of statements the strength of their preference towards one of the alternatives.

Following the same structure, the next step supports the consideration between surgery and radiotherapy. For surgery, three common methods are discussed (laparoscopic, open and robot assisted). For radiotherapy this consists of brachytherapy and EBRT. Again, information provision is followed by values clarification statements. The VCMs in this step emphasize the main differences between surgery and radiation therapy (both brachy and EBRT) in terms of treatment procedure (‘*I find it important that all cancer cells are removed from my body’* versus ‘*I find it important that the cancer cells die and not grow further*’), side effects (‘*I find bowel problems worse than incontinence*’ versus ‘*I find incontinence worse than bowel problems’*), secondary treatment (*‘I am comforted by the thought that I can have radiation if surgery is unsuccessful’* versus ‘*I accept that surgery is difficult after radiation’*) and fear for surgery (*‘I am not anxious about surgery’* versus *‘I am anxious about surgery’*). If a patient already indicated a preference for active surveillance in the previous step, the program allows patients to ignore this part and continue to the last step. As a conclusion, the final step asks patients to indicate their final treatment preference and briefly explain their choice. The DA does not provide treatment advice, but helps the patient to reach an informed preference. A summary then provides an overview of all answers to the statements and the patients’ final preference. To discuss this summary with their urologist, the summary can be printed or accessed online during the next consultation.

All statements used in the VCMs were developed by a team of urologists, psychologists and engineers based on previous experience and observation of conversations where treatment decisions were discussed. The statements were evaluated during usability-testing among patients, urologists and nurses (N = 10).

### Recruitment

Patients in both arms will be recruited by their treating urologist. When meeting the inclusion criteria, the urologist will use a letter and a leaflet, in which the study is clarified, to invite eligible patients to participate. The letter and accompanying leaflet about the study will state that we would like to investigate the information provision and decision-making process in general, without explicitly mentioning that a DA is the subject of this study. This reduces potential bias from emphasizing that the DA is an addition to usual care, as the perception of any addition to usual care may evoke improved satisfaction on itself. It will also avoid a situation where patients in the control group feel that they are withheld from a potential helpful tool. Patients are not informed about the randomization at the hospital level.

For all logistics involved to distributing and processing the questionnaires, the PROFILES-application will be used. ‘Patient Reported Outcomes Following Initial treatment and Long term Evaluation of Survivorship (PROFILES)’ is a registry for the study of the physical and psychosocial impact of cancer and its treatment from a dynamic, growing population-based cohort of both short and long-term cancer survivors. PROFILES was developed in 2009 by a joint research group from Tilburg University and Comprehensive Cancer Centre South (CCCS) with a grant from the Netherlands Organization for Scientific Research (NWO) [31]. PROFILES enables data collection management, from inviting patients to participate in studies to collecting patient-reported outcomes data via web-based or mailed questionnaires, and provides a supporting helpdesk. Patients can send their informed consent form, which they receive with the information letter to PROFILES. On the informed consent form patients can indicate whether they want to receive questionnaires via email or regular mail. Approximately 1 to 2 weeks after treatment decision-making (T1) patients receive either the invitation (email) to fill in an online questionnaire or a paper version at their home address. In the case of a paper version, a stamped self-addressed envelope is provided to the patient to return the questionnaire. If patients do not fill in their questionnaires within two weeks, a reminder letter or email will be send. Patients will be assured that nonparticipation does not result in differential follow-up care or treatment. The PROFILES-application allows for managing the follow-up questionnaires, which are sent at 6 and 12 months following T1.

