During the past decade, several decision aids (DAs) have been developed with a special focus on prostate cancer care. Instruments range from information booklets to tailored web-based tools. The variety in the formats used may have contributed to the finding that effects on decisional outcomes have been inconsistent across randomized trials and that no effects on choice have been found [21, 22]. Systematic reviews further emphasize that many previous studies are at high risk of selection bias due to inadequate concealment or blinding of data collectors and outcomes assessors, and that more studies are needed to determine how DAs can be implemented best in clinical practice [21, 22].

Determining the effect of a DA intervention and finding optimal implementation methods are both aims of the current trial. A web-based prostate cancer treatment DA was developed to fit with Dutch clinical workflow. Based on the structure of an existing DA developed by Feldman-Stewart and colleagues [23, 24], Dutch content was written and values clarification methods (VCMs) were added. Adaptation of the DA was based on the International Patient Decision Aid Standards (IPDAS) [25].

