### Randomization

Nineteen Dutch hospitals have been randomized to either ‘usual care’ (arm 1) or ‘usual care + DA’ (arm 2). With this so-called prerandomization, the conventional sequence of obtaining informed consent followed by randomization is reversed [29]. This prerandomization is needed because we make clinicians aware (when introducing the DA) of the principles of shared decision-making and the characteristics of the DA. This could affect the control group if they were recruited within the same hospital.

To prevent potential imbalance between the two arms that could arise from hospital characteristics (for example, hospital size and treatment profile), two strata were included in the randomization procedure. First, if cooperation between two hospital locations leads to overlap in medical staff or patients visiting both locations, there is a risk for contamination bias if these hospital locations are not in the same cluster. In our sample, four pairs of hospitals have this overlap in hospital staff or patient visits. To maintain variability in hospital characteristics within each cluster, only two pairs were allowed to enter the same cluster. The second criterion is related to hospital specific treatment variation. In The Netherlands, hospitals that perform robot-assisted radical prostatectomy indicate a significant larger proportion of their patients for surgery compared to other hospitals [4]. At the moment of randomization, three hospitals from our sample are known for having robotic surgery facilities to treat prostate cancer patients, and only two of these hospitals were allowed to join the same cluster.

Randomization was performed by a statistician not involved in the study and blind to the identity of the hospitals, using SPSS version 19.0 (Statistical Package for Social Sciences, Chicago, IL, USA). As a first step, the four paired hospitals were randomized (block size = 2). Next, the remaining 11 hospitals were also block randomized (block size = 6, with the last position unused). A set seed was chosen that fulfilled to the criteria that only two robot facilitated hospitals were allowed into the same cluster. The generated group order was then applied to a pre-existing list of participating hospitals, which was sorted in alphabetical order. As there is an uneven number of hospitals participating in this study, the largest cluster that was formed was identified as the intervention cluster.

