### Sociodemographic variables and additional healthcare utilization

Standard sociodemographics will be asked on age, marital status, occupation, and education. Also, patients will be asked to report any additional healthcare utilization (general practitioner or other medical specialist) in the past 12 months to assess whether this affects the decision-making process.

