### Statistical analysis

All analyses will be conducted using SPSS version 19.0 (Statistical Package for Social Sciences, Chicago, IL, USA). A 0.05-significance level will be adopted in all statistical tests.

We will perform a descriptive statistical analysis of organizational (hospitals) and socio-demographic (patients) characteristics in order to assure the comparability of the intervention and control groups. Baseline measures and changes in outcome variables over the study period for each study arm will be presented as means (± SD).

The main outcome decisional conflict is measured at T1 and will be compared between both groups (intervention and control). Multilevel modelling will be carried to take the hierarchical structure of the data into account by specifying random effects at both hospital and patient level. The least square mean proportions will be estimated and compared to assess the effect of the DA on decisional conflict.

The secondary outcomes will also be compared between both groups using multilevel modelling. Some of the secondary measures consist of repeated measures (for example, HRQoL and decisional regret) and will be treated according the appropriate mixed-model approach; that is, repeated measures anova/ancova will be used for outcomes with two time points (decisional regret, treatment satisfaction), and a random coefficient approach will be used for outcomes with three time points (HRQoL) [67]. Observed variation in treatment choice during the trial period will be compared between groups and at level of the individual hospital. For this second comparison, each hospital’s particular historical treatment variation profile (2008 to 2012) will be obtained from the Netherlands Cancer Registry.

Potentially confounding variables (for example, personality, health skills, and age) will be explored for their impact on the primary and secondary outcomes. Missing data and drop-outs will be described.

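### Patients are recruited after hospital allocation, by urologists who in the decision-aid arm know it, and the stated comparability check names no clinical case-mix variable

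*Protocol article*

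**What the plan says.** Under Randomization, the article explains that hospitals were allocated before any patient was approached, so that "the conventional sequence of obtaining informed consent followed by randomization is reversed". The reason given is contamination: "we make clinicians aware (when introducing the DA) of the principles of shared decision-making", which could spill over to controls treated in the same hospital.

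Under Recruitment, "Patients in both arms will be recruited by their treating urologist". The masking described there is on the patient side: the letter and leaflet do not name the DA as the subject of the study, and "Patients are not informed about the randomization at the hospital level".

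Under Intervention, the clinical characteristics appear on the DA access card: "patients receive a card from their urologist stating their relevant disease characteristics (PSA, Gleason, and eligible treatment options". Neither Table 1 nor Table 2 lists PSA, Gleason, risk group or eligible options.

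Under Statistical analysis, the plan is a "descriptive statistical analysis of organizational (hospitals) and socio-demographic (patients) characteristics in order to assure the comparability of the intervention and control groups". The patient part is spelled out elsewhere: "Standard sociodemographics will be asked on age, marital status, occupation, and education".

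**The concern.** Randomizing hospitals balances hospitals in expectation. It does not protect the make-up of the patients enrolled later if the person who invites them knows the arm. DA-arm urologists must know it, because they are introduced to the DA and supply the details for its access card. Part of eligibility is also their judgement, since a man must qualify for at least two of the listed treatment options. Clinicians newly introduced to shared decision-making could apply that criterion differently, or could invite different men.

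Disease risk bears directly on which treatment is chosen and plausibly on how hard the decision feels. If the mix of low- and intermediate-risk men differed between arms, part of any difference in decisional conflict or treatment choice would come from recruitment and not from the DA. The table intended to show that the arms are comparable contains nothing that would reveal this.

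**Working it through.** **Setting the sections side by side**

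1. Order: hospitals allocated, then patients invited (Randomization, Recruitment).
2. Knowledge of arm: certain for DA-arm clinicians (Randomization, Intervention). For control urologists it is an inference; no masking is described.
3. Safeguards on selection: the article describes no arm-blind recruiter, consecutive-invitation rule or count of eligible men. DA-arm providers are asked afterwards whether they offered the DA to all eligible patients (Healthcare providers' evaluation). No matching question on invitations is described for controls.
4. Variables in the check: hospital characteristics plus age, marital status, occupation and education.
5. Possible substitutes: every patient questionnaire starts at T1, one to two weeks after the decision and hence after DA exposure. Health numeracy and literacy come at T2. No patient-reported pre-exposure baseline can stand in for clinical case mix.

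**Size, if recruitment did differ (shift sizes are assumptions)**

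Inputs from Sample size calculation: 19 hospitals of 20 patients (380), ICC 0.01, alpha 0.05 (taken as two-sided). From Randomization: four pairs split two and two, 11 single hospitals split 6 and 5, larger group to the DA, so 10 against 9 hospitals, or 200 against 180 patients.

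- Design effect = 1 + (20 − 1) × 0.01 = 1.19
- SE = √[1.19 × (1/200 + 1/180)] = 0.112 SD

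The plan's own power figure does not reproduce from these inputs: Φ(0.50/0.112 − 1.96) = 0.994, against the stated 0.80. That is a separate matter, and nothing here depends on it.

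With a true effect of zero and a recruitment-induced shift b in mean decisional conflict, P(reject) = Φ(b/SE − 1.96) + Φ(−b/SE − 1.96):

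| Assumed shift b (SD) | P(false positive) |
|---|---|
| 0 | 5.0% |
| 0.05 | 7.3% |
| 0.10 | 14.5% |
| 0.20 | 43.0% |
| 0.30 | 76.3% |

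A shift of 0.10 SD would arise if a patient type whose decisional conflict differs by 0.5 SD were 20 percentage points more common in one arm: 0.20 × 0.5 = 0.10.

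For treatment choice, suppose 70% of enrolled DA-arm men but 60% of controls had active surveillance as an option, and half of those chose it. Uptake would differ by (0.70 − 0.60) × 0.50 = 0.05 with no DA effect. Using the same patient numbers and design effect, and an assumed 40% choosing a given option in one arm, the chance of a significant result is Φ[(Δ − 1.96 × SE₀)/SE₁], with SE₀ pooled and SE₁ unpooled. It is about 14%, 43% and 77% for Δ of 5, 10 and 15 points.

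**The case against.** The design has a stated justification. Clinicians who hand out a DA cannot be masked to it, and randomizing patients within hospitals would contaminate controls. Hospital allocation was made by an uninvolved statistician blind to hospital identity, and the neutral letter limits bias on the patient side. All of this stands; the cluster design is not the defect.

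The eligibility criteria apply in both arms. They restrict enrolment to low or intermediate risk and exclude PSA of 10 or more combined with Gleason 7, which narrows the possible imbalance. It does not remove it, because the mix of low and intermediate risk can still differ. The same criteria mean that control urologists must already know these values, so the values may be stored somewhere a condensed article does not mention. The point is therefore limited to what the article does fix: the content of the comparability check and the place where clinical values are recorded.

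A reader might infer that bias would pass entirely undetected. That goes too far. The plan explores potential confounders through an open list of examples that includes age, personality and health skills, and the Discussion allows adjustment for hospitals' past treatment profiles. The first looks at impact on outcomes and not at balance of disease risk. The second is optional, at hospital level and historical. They weaken the word undetected but do not fill the gap.

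A reader might also infer that this is the very fault the Background finds in earlier trials, where "many previous studies are at high risk of selection bias due to inadequate concealment". That sentence goes on to blinding of data collectors and outcome assessors and does not discuss recruitment in cluster trials. The two are related, but the text does not equate them.

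**Conclusion.** The point holds as a risk that the plan can cheaply reduce. Allocation precedes recruitment, the recruiter in the DA arm knows the allocation, and the check as written would not show a clinical case-mix difference. The documents give no evidence that differential recruitment took place, and control urologists' awareness of their arm is inferred.

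The consequence should not be stated as bias in two primary outcomes. Decisional conflict is the only primary outcome. Treatment choice is classed as secondary, although the main objective names it.

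The size depends entirely on assumed shifts. Across 0.05 to 0.30 SD in decisional conflict, the false-positive rate runs from about 7% to 76%; for differences of 5 to 15 points in treatment choice, it runs from about 14% to 77%. These figures assume 380 analysed patients, equal hospital sizes and an ICC of 0.01. A small imbalance would matter little and a moderate one a good deal, which is reason enough to measure it.

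**What to change.** 1. Record PSA, Gleason and risk group for every enrolled patient in both arms. Recruitment is under way, so for control patients already enrolled these values would be retrieved from the hospital record, after checking that their consent covers it.
2. Add these variables to the comparability table, by arm.
3. Prespecify age, PSA and Gleason or risk group as fixed covariates in the multilevel models for decisional conflict and treatment choice.
4. Report eligible treatment options by arm descriptively, or use them in a sensitivity analysis only. Clinicians list them after allocation and the arm may influence the list, so adjusting for them in the main model could remove part of the DA effect or add bias.
5. Where feasible, keep a simple count of eligible and invited men per hospital and report the enrolled fraction by arm. The registry should not be relied on for this: the article uses it for hospital treatment profiles, and nothing shows that it can identify men who meet the trial's criteria on options, internet access, cognition and language.

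The cost is a small amount of clerical work per control patient, plus the retrieval for those already enrolled. The limit is that adjustment deals only with measured characteristics. If urologists selected on preference or motivation, the models would not correct it, and the counts in step 5 would be the main warning sign.

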### Outcome measures

Table 1 shows an overview of all outcome measures and the moment of measurement.

**Table 1 Tab1:** Outcome measures

Outcomes	Instrument	T1	T2	T3
Shared decision-making outcomes				
Decisional conflict	Decisional Conflict Scale	X		
Decisional regret	Decisional Regret Scale		X	X
PrCa Knowledge	PrCa decision quality instrument	X		
Satisfaction with information	SCIP-B	X		
Decision-making preparedness	Preparation for DM-scale	X		
Decision-making role	PSDM-scale	X		
Perceived doctor-patient relationship	Single item	X	X	X
Actual treatment choice and health outcomes				
Initial preference and treatment choice	Single items	X		
Treatment satisfaction	Single item		X	X
Health-related Quality of Life	EORTC QLQ-C30	X	X	X
	EORTC QLQ-PR25	X	X	X
Side-effect impact	IIQ-7 subset for emotional state		X	X
Acceptance & Control over health status	Subjective experienced health (SBG)	X	X	X

### Primary outcomes

Primary outcome is decisional conflict. The decisional conflict scale (DCS) [32, 33] evaluates the level of decisional conflict on five subscales; the feeling of being well-informed; the clarity of values; the feeling of support during the decision-making process; the feeling of uncertainty about best choice; and the effectiveness of the decision. The level of decisional conflict is measured at T1. The DSC is widely accepted and applied as main outcome measure in (PrCa) DA trials [24, 34–36].

### Secondary outcomes

Secondary outcome measures can be categorized as either shared decision-making outcomes or health outcomes. Shared decision-making outcomes consist of decisional regret [37], perceived and preferred decision-making role [38], and preparation for decision-making to assess a patient’s preparation for decision-making and dialoguing with his clinician [39]. Furthermore, a single-item question will evaluate the perceived patient-doctor relationship and the development of this relationship over time. Also, satisfaction with information provision [40] and knowledge [41] will be assessed.

Health outcomes refer to the actual treatment choice and any changes in treatment preference during the decision-making process. Treatment satisfaction will be measured with a single-item question: ‘Are you satisfied with the way your treatment was or is executed?’ To assess health-related quality of life (HRQoL) the EORTC QLQ-C30 [42] will be used. This questionnaire is developed specific to assess HRQoL in cancer patients. Much of the content of the questionnaire is appropriate for extended monitoring of health status, including scales assessing physical, role, cognitive and emotional functioning, fatigue and sleep problems, and overall health and quality of life. This core instrument is supplemented with the prostate cancer-specific HRQoL questionnaire EORTC QLQ-PR25 [43]. This 25-item questionnaire assesses urinary, bowel and sexual symptoms and functioning, and the side-effects of hormonal treatment, though hormonal treatment is not offered as initial treatment in this study’s sample. Health outcomes are further assessed by means of an evaluation of side-effect impact [44, 45] and health status acceptance and subjective control [46].

